**The following are methodologies undertaken throughout the duration of the study.**

## **III. Physical measurements**

Body mass index and waist and hip circumference measures will be used to assess the body composition of the participants.

#### IV. Blood Collection for genotyping and biomarker analyses.

It is intended that blood samples will be collected within the same time period at every participant visit in an attempt to account for any biomarker circadian variation. Trained study investigators will collect a blood sample from participants. A total of 37 mls of whole venous blood will be collected at the baseline visit and 27 ml will be collected during the two follow-up visits.

Apolipoprotein E (APOE) genotyping: We will be determining the APOE genotype in our study population for three reasons. First, it allows us to investigate whether APOE status is a shared risk factor underlying stroke and dementia. Second, we need to know whether APOE is potential confound against the utility of exercise intervention on neurodegenerative processes. Third, given its strong relationship to Alzheimer's Disease, an inadvertent over-representation of APOE  $\epsilon$ 4 homozygosity would act as a potential confound for our study.

Two 5 ml vacutainer tubes of venous blood will be taken during the first, second, or third testing session (i.e., 2, 4, or 12 months post-stroke) for genetic analysis. One sample will be used for APOE genotyping and the second will be used for genetic analyses by the study investigators.

Participants will have the option of being informed about their APOE  $\epsilon$ 4 status. It will be explained to stroke participants that this may have been a risk factor for their stroke. Participants who have APOE  $\epsilon$ 4 homozygosity will be offered counselling via the Neurogenetics Clinic at Austin Health if they have further questions or concerns, or if their family members have questions.

APOE Analysis techniques: Genomic DNA (50 ng) is extracted using the Genomic-tip 20G (Qiagen, Hilden, Germany) and the APOE region of interest will be amplified with specific primers (Invitrogen, Carlsbad, CA). The resulting DNA fragment will be sequenced with BDV3.1 (Applied Biosystems, Foster City, CA) using the APOE-forward primer on an ABI 3130-xl genetic analyzer.

BDNF and HbA1c: Of the whole blood drawn, 9 mls will be collected in a plain tube, allowed to clot for at least 20 minutes at room temperature, and then centrifuged. The serum will be divided into 4 x 1.5 ml tubes for storage at -20°C until assayed. The remaining 18 mls will be collected in lithium heparin/EDTA tubes, stored on ice, and centrifuged within 15 minutes to separate the plasma. Plasma will be aliquoted into 8 x 1.5 ml tubes and storage at -80°C until assayed.

The samples will be split in two so that two separate freezers contain the samples. This is performed so that if for any reason one freezer has a fault that thaws the sample, a backup sample is still available for analyses. The freezers will both be locked. All sample tubes will only contain the ID number of the participant and date of collection and will contain no names.

Planned exploratory analysis will include BDNF and HbA1c assays on sample batches. A HbA1c tube is taken at each timepoint assessment alongside additional research blood samples. We anticipate that most samples will be collected at the baseline session by a

trained investigator or stroke research nurse at The Florey or Sunshine Hospital.

Inflammatory marker assays: Blood plasma samples will be transferred from The Florey (Melbourne Brain Centre) to Monash University for analysis by [name] and her laboratory team. This will include a multiplex panel of 6 biomarkers: IL-6, IL-1 $\beta$ , TNF- $\alpha$ , IL-8, IL-10, and IL-1ra (Method: Multiplex ELISA (Millipore). Monash University will be provided with the results of these analyses once they are completed.

It is possible that unused portions of blood samples collected in the current study will be tested for other biological markers at some stage in the future. However, such analysis is not an immediate focus of the study protocol. Any further analysis of blood samples not detailed in this Protocol will be raised with Austin Health HREC if/when that time arises.

## **V. Ambulatory Blood Pressure and ECG monitoring**

24-hour ambulatory BP monitoring and 15-minute ECG-based heart rate variability for autonomic nervous system function assessment will be conducted for each assessment visit. Each participant will have a CardXplore monitor fitted for 24 hours. The CardXplore is a combined 24-hour ambulatory blood pressure and Holter ECG recorder. Trained staff will fit the monitor and explain the procedure to the participant. Analyses will be undertaken with the guidance of Associate [name] [name] in Clinical Pharmacology.

Circadian BP pattern classification will be based on the per cent decline in night-time BP compared with daytime BP. The normal ranges of ambulatory BP are defined as follows: daytime BP <135/85 mm Hg, night-time BP <120/75 mm Hg, 24-hour BP <130/80 mm Hg. For secondary hypotheses, statistical analysis will be performed using BP as a binary variable; i.e., abnormal BP, yes/no.

CardXplore monitors will be fitted during the first part of each timepoint so that the participant can return the monitor during the second part of each timepoint, which will minimise inconvenience to participants.

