### **Secondary hypothesis**

- i. Brain volume will be correlated with BP and incident brain infarction at 4 months and 1 year post-stroke;
- ii. Incident end-organ disease (silent or recurrent brain infarction, ambulatory blood pressure (BP), and cardiac structural disease) at 4 months and 1 year post-stroke will be reduced by aerobic exercise;
- iii. Incident physical activity levels, normotension, normal cardiac indices, higher aerobic capacity, and better sleep profiles will be associated with preserved brain volume at 4 months and 1 year post-stroke.

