## **b. STUDY AIMS**

Using brain volume and brain connectivity measures at one year after stroke, the aims of this research project are:

1. Examine the effects of home-based aerobic exercise intervention delivered at 2 months post-stroke on brain volume 4 months after stroke, and the stability of such effects at 1 year after stroke;
2. Document vascular burden using 3 end-organ effects: incident brain infarction, cardiac diastolic dysfunction, and ambulatory BP;
3. Examine the link between incident physical activity, aerobic fitness, sleep, and brain volume;
4. Examine the effects of exercise on blood pressure and cardiac diastolic function 4 months and 1 year after stroke;
5. Measure the change in BDNF and HbA1c levels 4 months and 1 year post-stroke and if exercise affects these;
6. Examine the association between physical activity, dietary intake, gut microbiome and brain volume.

An additional aim, which has been framed as a sub-study nested within the greater protocol, will enable us to capture any specific factors that influence participation in, or adherence to, post-stroke home-based exercise regimens.

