## **c. OUTCOME MEASURES**

Our primary outcome measure is:

- Brain volume at 4 months post-stroke.
- Our secondary outcome measures are several end-organ disease measures:
  - Silent or recurrent brain infarction;
  - Cardiac diastolic function;
  - Ambulatory BP;
  - Blood BDNF and HbA1c;
  - Sleep duration, variability, efficiency, and onset latency;
  - Dietary intake and gut microbiome
- Qualitative:
  - Understand the feasibility of prescribing post-stroke home-based exercise.

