### Timelines and feasibility

The 8 week intervention will commence at 2 months after stroke (see Figure 1. Experimental design and participant timeline). At the 2 month, 4 month, and 1 year post-stroke time-points,

we will capture brain images with MRI, perform ambulatory BP measurements and cognitive testing, assess aerobic capacity, fit Actiwatches, deliver the 7-day Sleep Diary and sleep questionnaire, and explain how to use the Research Food Diary app (sleep and dietary assessments to be completed at home). Blood samples will be collected at each time-point to check for concurrent changes in levels of BDNF and HbA1c. Additional blood (10ml) will be collected at the first (2 months post-stroke), second (4 months post-stroke), or third (12 months post-stroke) to test for APOE status and genetic risk. Stool samples will be collected by participants at home after each time point and they will be returned by the participant to the study site with the 24-hour BP device.

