#### c. STATISTICAL METHODS TO BE UNDERTAKEN

The analysis can be considered in 3 parts, aligned with primary and secondary hypotheses:

- i. **Primary outcome and hypothesis: Comparing brain volumes between stroke participant groups:** Primary outcome will be analysed on an intention to treat basis, The difference in brain volume from baseline to 4 months will be analysed using an ANCOVA model with exercise intervention group as a factor (e.g., Physical fitness training vs. Balance training groups), with baseline brain volume and functional status as co-variants (dichotomised as mRS = 0-1, 2 and 3).
- ii. **Secondary outcome and hypotheses: Correlating brain volume with blood pressure control and incident stroke:** Secondary outcomes will be analysed using appropriate repeated measures random effect logistic regression models with dichotomised hypertension status or silent/recurrent brain infarction (as defined in methods) as dependent variables, treatment group as independent variable, and functional status dichotomized as a covariate (as above). The initial regressive analysis will examine the

differences between participants with good and poor blood pressure control, using this as a binary measure. The presence of incident subclinical stroke will also be included as a binary variable. In the regional volumetric analyses, total brain volume, regional white matter, cortical and subcortical grey matter volume changes will be modelled using this design.

- iii. **Exploratory analyses: Independent effects of exercise on blood pressure, incident stroke, diastolic cardiac indices, and aerobic capacity:** Exercise effects on end-organ function and fitness (i.e., aerobic capacity) are likely dissociable, however emphasise that this component is exploratory. For the purposes of these analyses, we define each of our end-organ metrics as: brain volume, cognitive function, incident stroke, diastolic cardiac indices, aerobic capacity (VO2max), sleep duration, onset latency, bedtime/rise time variability (minutes), and sleep efficiency (%). Exploratory analysis will be conducted using appropriate regression models to investigate the associations between BP, incident stroke, diastolic cardiac indices, aerobic capacity. In addition, mediation analyses will be conducted to explore the possible mediating role of sleep in preservation of brain volume.

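### For the secondary hypotheses, ambulatory BP is analysed as abnormal yes/no with no continuous analysis and no baseline BP term named, which discards much of the information already collected

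*Protocol*

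**What the plan says.** Ambulatory BP is a named secondary outcome (Protocol 4.c), in a list introduced by "Our secondary outcome measures are several end-organ disease measures". Secondary hypothesis ii (4.a) states that incident end-organ disease, with ambulatory BP among its components, "at 4 months and 1 year post-stroke will be reduced by aerobic exercise". Hypothesis i relates brain volume to BP. Aim 4 (4.b) is to "Examine the effects of exercise on blood pressure and cardiac diastolic function 4 months and 1 year after stroke".

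On measurement, section 5.d.V states: "24-hour ambulatory BP monitoring and 15-minute ECG-based heart rate variability for autonomic nervous system function assessment will be conducted for each assessment visit". The timelines in 5.a place these recordings at 2 months (baseline), 4 months and 1 year.

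On analysis, section 5.d.V says that for the secondary hypotheses "statistical analysis will be performed using BP as a binary variable; i.e., abnormal BP, yes/no". Section 8.c.ii specifies repeated-measures random-effect logistic models with dichotomised hypertension status as a dependent variable, "treatment group as independent variable, and functional status dichotomized as a covariate (as above"). It goes on: "The initial regressive analysis will examine the" contrast between good and poor BP control, again as a binary. The regional brain-volume analyses are to follow the same design.

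By contrast, the primary ANCOVA in 8.c.i includes baseline brain volume as a covariate. Section 8.c.iii plans exploratory regressions involving BP and does not say whether BP enters as continuous or binary.

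**The concern.** A 24-hour recording yields BP in mm Hg. Reducing it to abnormal yes/no gives a change of 1 mm Hg across the threshold the same weight as a change of 20, and gives no weight to a change that stays on one side. Each participant also has a pre-randomisation recording that predicts later BP, yet the named model terms do not include it.

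At stake is the ability of a trial of 120 to show an exercise effect on BP (hypothesis ii, aim 4), and to relate BP to brain volume (hypothesis i), where the same binary is the BP variable. This is a rule the protocol states in two sections, not a detail left open. An analysis plan that made a continuous BP analysis the main one for these hypotheses would depart from the protocol.

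**Working it through.** **The plan's own figure.** No sample size or power is given for BP. Section 8.b covers brain volume: d = 0.6, two-sided 0.05, 80% power. That gives 2(1.96 + 0.842)²/0.6² = 43.6, so 44 per group; 44 × 1.3 = 57.2, so 58, close to the stated 60. Removing 30% from 60 leaves 42 per group, used below.

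**Assumptions not in the protocol.** BP approximately normal with equal SDs; share of controls abnormal p; equal correlation ρ between any two visits; a constant shift d (in SDs) at both follow-up visits.

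**Step 1: the split alone, at one visit.** Relative efficiency is E = φ(z)²/[p(1−p)], with z the normal cut-point.
- p = 0.5: 0.3989²/0.25 = 0.637, a loss of 36%. This is the minimum over all cut-points.
- p = 0.3 (or 0.7): 0.3477²/0.21 = 0.576, a loss of 42%.
- p = 0.2 (or 0.8): 0.490, a loss of 51%.

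**Step 2: omitting baseline as well, at one visit.** Baseline adjustment multiplies the continuous variance by 1 − ρ². The unadjusted binary analysis then keeps E(1 − ρ²) of the information:
- p = 0.5: 0.637 × 0.75 = 0.48 at ρ = 0.5, and 0.637 × 0.51 = 0.32 at ρ = 0.7.
- p = 0.3: 0.43 and 0.29.

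**Step 3: both follow-up visits, as in the repeated-measures model** (42 per group, p = 0.5). Yes/no responses correlate less across visits than the underlying BP does: ρ_b = (2/π)·arcsin ρ, which is 0.333 at ρ = 0.5 and 0.494 at ρ = 0.7. Pooling visits therefore recovers a little. The loss from the split alone becomes 1 − 0.637 × 1.5/1.333 = 28%, and 1 − 0.637 × 1.7/1.494 = 28%.

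Power is Φ(effect/SE − 1.96).
- *Binary, no baseline.* Share abnormal falls from 0.50 to 0.345 (d = 0.4) or 0.274 (d = 0.6), log odds ratios −0.641 and −0.974. Variance is [(1 + ρ_b)/2] × [1/(42 × 0.25) + 1/(42 × p₁(1 − p₁))]. For d = 0.4 and ρ = 0.5: 0.667 × 0.2006 = 0.1337, SE 0.366, ratio 1.75, power 42%.
- *Continuous, no baseline.* SE = √(2V/42), with V = (1 + ρ)/2 = 0.75 or 0.85.
- *Continuous, with baseline.* V = (1 + ρ)/2 − ρ² = 0.50 or 0.36. For d = 0.4: 0.4/0.1543 = 2.59, power 74%; 0.4/0.1309 = 3.06, power 86%.

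| Analysis (ρ = 0.5; ρ = 0.7) | d = 0.4 | d = 0.6 |
|---|---|---|
| Binary, no baseline | 42%; 38% | 73%; 68% |
| Continuous, no baseline | 56%; 51% | 89%; 85% |
| Continuous, with baseline | 74%; 86% | 97%; over 99% |

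Simulation of the same setting, with a GEE logistic model standing in for the random-effect model, gave about 41-43% and 70-76% for the binary analysis and about 74-88% and 97-99% for continuous with baseline. The two methods agree to within about 3 points.

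**The case against.** Several points on the other side are sound.

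- *BP may not be analysed only as a binary.* Section 5.d.V confines the rule to the secondary hypotheses, 8.c.ii calls the good/poor contrast the initial analysis, and 8.c.iii leaves the form of BP open. A reader might infer that no continuous BP analysis can ever be done. The text does not go that far. What stands is that none is named for the secondary hypotheses, and an exploratory regression cannot carry them.
- *The baseline recording may be used.* In a repeated-measures model, baseline could enter as an outcome row, so it cannot be said that baseline BP is unused. But no time or group-by-time term is named. A single treatment term spread over a pre-randomisation visit would dilute the effect rather than adjust for baseline.
- *A one-visit power comparison overstates the gap.* A single-visit logistic test at 0.4 SD has about 31% power. A reader might set that against a baseline-adjusted continuous model, but the protocol's model is repeated-measures, so step 3 uses both follow-up visits.
- *42 per group is borrowed.* The 30% allowance in 8.b also covers unusable scans and runs to 12 months. It is therefore conservative for BP, particularly at 4 months.
- *A threshold has a clinical basis.* The hypotheses speak of end-organ disease and normotension. This makes the binary a reasonable supportive result. It does not recover the lost information.
- *No single BP measure is favoured.* Section 5.d.V lists daytime, night-time and 24-hour limits, systolic and diastolic, and the background in 3.c highlights evening diastolic BP. The documents do not support naming 24-hour systolic BP as the right one.

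**Conclusion.** The point holds as an inefficient analysis rule that the protocol fixes. It is not an error or a contradiction. For the secondary hypotheses, BP is a yes/no outcome, with neither a continuous analysis nor a baseline BP term named.

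The 36% minimum loss at a given visit needs only approximate normality and a modest shift. The loss from the split alone is about 28% when two visits are pooled with half abnormal. The wider gap, about 41-43% against 74-88% power at 0.4 SD and 70-76% against 97-99% at 0.6 SD, combines the split with the missing baseline adjustment and depends on the assumed share abnormal, correlation, shift and 42 per group. The protocol supplies no BP effect size; its d = 0.6 refers to brain volume.

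The primary analysis is unaffected and no power is claimed for BP. The change is worth making because it strengthens a stated secondary hypothesis using data already planned.

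**What to change.** Reword sections 5.d.V and 8.c.ii as follows.

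1. For hypothesis ii, make the main BP analysis a linear mixed model or ANCOVA of one prespecified continuous ambulatory BP measure, chosen by the sponsor (a 24-hour mean, for example), at 4 and 12 months, with treatment group, the baseline value of that measure and mRS group.
2. For hypothesis i, use the same continuous measure as the BP variable in the brain-volume models.
3. Keep abnormal yes/no as a supportive analysis, adjusted for baseline.

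The cost is a change of wording and slightly more analysis work, with no new data or visits. The headline BP result becomes a difference in mm Hg and is less directly tied to a threshold, but the yes/no result is still reported beside it.

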## **VI. MR Image Acquisition, Processing, and Analysis pipeline**

High resolution structural magnetic resonance imaging (MRI) of study subjects will be acquired using a 3T clinical MR scanner. High resolution 1 mm isotropic T1-weighted 3D MP-RAGE, T2 FLAIR and T2 3D images will be acquired. Other images to be acquired in the same scanning session: Diffusion weighted image (DWI) to check for recent stroke; susceptibility weighted image (SWI) to check for microbleeds; a "free run" EPI scan (approximately 7 minutes) for connectivity analysis, and an arterial spin labelling sequence (approximately 10 minutes) to measure cerebral blood flow. Total scan time will be approximately 65 minutes.

Recurrent stroke will be assessed on imaging characteristics at each MRI: Intercurrent stroke between scanning intervals will be diagnosed by 2 neurologists on inspection of FLAIR, T1 and T2 images for stroke < 10 days old. DWI images will be inspected for recent stroke. These will be manually traced and masked for future analyses, and all stroke volume calculated for later use in exploratory analyses. For secondary hypotheses, presence of

recurrent stroke (clinical or silent) will be dichotomised as a binary variable; i.e., recurrent stroke: yes/no (see statistical analyses).

Structural analyses: cortical thickness and white matter hyperintensity volume: Cortical thickness will be mapped using the FreeSurfer software package for analysis of structural MRI [33]. Hippocampal volume estimation will be performed using Adaboost, which has been shown to have ICCs of 0.94-0.96 with manual tracing [34]. We will use QUANTA for WMH segmentation and estimation.

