### ***Time Period, Frequency, and Method of Detecting AEs and SAEs***

All AEs and SAEs will be recorded from the time of consent until the final follow up visit at one year post-stroke. Each participant will be monitored regularly by the investigator and study personnel for events occurring throughout the study.

During the study, the investigator will enquire about AEs by asking the following non-leading questions:

*"How are you feeling?"*

At subsequent scheduled intervals participants will be asked:

*"Since you were last asked, have you felt unwell or different from usual?"*

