#### d. REPLACEMENTS

As discussed below in Section 8.a (Power Calculations), we expect around 30% attrition due to death or non-participation (e.g., unable to participate in testing due to new pacemaker/implanted metal/other medical issue, lost to contact, not interested). This has been taken into account in our sample size estimation and power analysis, and so, the statistical significance of the sample size is unlikely to be affected by participant withdrawal.

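### Recurrent stroke is labelled clinical or silent, but the only stated rule for finding it is the study MRI, so a clinical stroke with no later scan is not counted in this secondary outcome

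*Protocol*

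**What the plan says.** Section 4.c lists "Silent or recurrent brain infarction" as a secondary outcome, and secondary hypothesis ii (section 4.a) expects aerobic exercise to reduce it at 4 months and 1 year.

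Section 5.d.VI gives the ascertainment rule: "Recurrent stroke will be assessed on imaging characteristics at each MRI". Two neurologists make the diagnosis from the study images. The same section then states the scope: "recurrent stroke (clinical or silent) will be dichotomised as a binary variable; i.e., recurrent stroke: yes/no".

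Section 8.c.ii enters "silent/recurrent brain infarction (as defined in methods) as dependent variables" in a repeated-measures random-effect logistic model, with treatment group as independent variable and dichotomised functional status as covariate. It gives no second definition.

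Section 7.d expects about 30% attrition. The reasons are death and non-participation, the latter illustrated by "unable to participate in testing due to new pacemaker/implanted metal/other medical issue, lost to contact, not interested".

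Section 7.b states: "All AEs and SAEs will be recorded from the time of consent until the final follow up visit at one year post-stroke". For each event the investigator reviews hospital and diagnostic records. A stroke that is fatal or leads to hospital admission meets the protocol's definition of a serious adverse event.

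**The concern.** The label and the rule do not match. The label promises clinical strokes; the rule finds them only if a study scan follows. No section lets a hospital diagnosis, a non-study scan or a death from stroke set the variable to 'yes', and nothing links the adverse-event records to it.

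The cases at risk are foreseeable. Death and medical inability to be tested are among the attrition reasons that the protocol itself names, and a new clinical stroke can lead to either. For those participants missingness depends on the outcome. The model in 8.c.ii contains treatment group and functional status but not the clinical event, so it cannot be relied on to recover them. The strokes lost this way would tend to be the more severe ones, in an outcome with few events to begin with.

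**Working it through.** **The protocol's own figures.** No event rate, power or sample size is stated for recurrent stroke. The only design figure is 60 per group for brain volume. It reproduces: 2 × (1.96 + 0.84)² / 0.6² gives 44 per arm (45 with the t distribution), and × 1.3 gives 58 or 59. This point does not affect it.

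**Inputs for the illustration.**
- L = 30% without the later scan (sections 7.d and 8.b), so 36 of 120 unscanned and 84 scanned.
- c = clinical recurrence after baseline: *assumed* 3%, 6% or 10%.
- s = silent infarction without clinical recurrence: *assumed* 10%.
- m_c = share of clinical recurrences with no later study scan: *assumed* 40%, 60% or 80%.
- m_o = share of all other participants unscanned, set so that the total is 30%: m_o = (L − c·m_c)/(1 − c).

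**Proportion under the MRI-only rule.** Observed = [c(1 − m_c) + s(1 − m_o)]/(1 − L); true = c + s.
- Central case (c = 6%, m_c = 60%): m_o = (0.30 − 0.036)/0.94 = 0.281. Observed = (0.024 + 0.0719)/0.70 = 13.7%, against 16.0% true, about 14% too low.
- Low end (c = 3%, m_c = 40%): m_o = 0.297. Observed = (0.018 + 0.0703)/0.70 = 12.6%, against 13.0%, about 3% too low.
- High end (c = 10%, m_c = 80%): m_o = 0.244. Observed = (0.020 + 0.0756)/0.70 = 13.7%, against 20.0%, about 32% too low.

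**In participants, central case.** 120 × 0.06 = 7.2 clinical strokes, of which 7.2 × 0.6 = 4.3 are not counted. At the background loss of 28.1%, 2.0 would be lost anyway, so the excess is about 2.3 (0.4 to 6.7 over the grid). Unscanned clinical strokes make up 0.036/0.30 = 12% of all missing scans.

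**Comparison between arms.** Take assumed true risks of 10% (balance) and 5% (fitness), a risk ratio of 0.50. Let q be the share of strokes unscanned in each arm, with 30% unscanned overall in both; observed risk = p(1 − q)/0.70.

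| q balance | q fitness | Observed risks | Risk ratio |
|---|---|---|---|
| 0.5 | 0.5 | 7.1% vs 3.6% | 0.50 |
| 0.5 | 0.3 | 7.1% vs 5.0% | 0.70 |
| 0.3 | 0.5 | 10.0% vs 3.6% | 0.36 |

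**Would one either/or variable repair it?** Central case, counting 'yes' for a new infarct on MRI or a documented clinical stroke. The 'yes' share of all randomised is 0.06 + 0.0719 = 0.1319.
- Unscanned participants without clinical stroke left missing: 0.1319/(0.06 + 0.94 × 0.719) = 0.1319/0.736 = 17.9%, about 12% too high, because unscanned people enter only as 'yes'.
- The same participants coded 'no': 13.2%, about 18% too low.

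Neither coding returns 16.0%, and the second is further off than the MRI-only rule.

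**The case against.** Section 5.d.VI describes the imaging pipeline, so it is natural that it speaks of scans; it nowhere says that MRI is the sole source. A scan alone cannot show whether an infarct was symptomatic, so the words clinical or silent suggest that clinical information was meant to be used. Building a derived variable from several records is often left to the analysis plan. An imaging endpoint is also defensible for an outcome described as infarction, with clinical strokes reported as safety events.

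Part of this stands. The defect is a missing link, not a rule that deliberately discards clinical strokes, and the events are not lost to the trial. It does not remove the point, because the protocol fixes a definition and 8.c.ii refers back to it. An MRI-only endpoint would be coherent if the label said so.

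Three stronger readings are tempting and not supported:
- *That clinical strokes in general go uncounted.* One followed by a study scan can still be detected, and one read at 4 months stays counted if the 12-month scan is missed. The loss is confined to strokes with no later study MRI. Whether the wording "inspection of FLAIR, T1 and T2 images for stroke < 10 days old" narrows what is counted on a completed scan is a separate question.
- *That the 30% attrition consists of such cases.* Section 7.d also lists loss of contact and lack of interest, and 8.b adds non-evaluable scans. In the central case, 12% of missing scans are clinical strokes.
- *That the treatment effect is biased.* Equal loss leaves the risk ratio at 0.50. Differential loss is possible, but the protocol gives no evidence of it.

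**Conclusion.** The point holds as a mismatch between label and rule in a secondary outcome. As written, a documented clinical stroke after baseline with no later study MRI does not count as recurrent stroke.

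The understatement of the proportion, about 3% to 32% with 14% in the central case, rests on assumed rates; only the 30% attrition comes from the protocol. The calculation treats follow-up as a single later scan, so it makes no allowance for silent infarcts already read at 4 months in people who miss the 12-month scan. Equal loss across arms mainly costs events and precision; bias in the comparison needs loss that differs by arm.

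A reader might infer that adding the adverse-event records to the existing yes/no variable settles the matter. The arithmetic shows that it does not: the pooled variable gives 17.9% or 13.2% against 16.0%, depending on how unscanned participants are coded. Separate components are what make this a worthwhile improvement, and a cheap one.

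**What to change.** Amend 5.d.VI and 8.c.ii to define and analyse two components, each with its own denominator:

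1. **Clinically documented recurrent stroke after baseline**, from adverse-event and hospital records, in all randomised participants for the time they were followed for events, whether or not an MRI was done. The two neurologists already reading the scans classify the records blind to group. State which stroke types count, since section 4.c speaks of infarction.
2. **New infarct on follow-up MRI**, among participants scanned, described as conditional on having a scan.

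Say that one stroke may appear in both. Do not pool the components into one yes/no variable in which unscanned participants can enter only as 'yes' or are coded 'no' by default. If a composite is kept, show it as a sensitivity analysis under both codings.

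The cost is wording in two sections, some extra record classification, and two low-count components in place of one binary outcome. No new data are needed. Participants lost to contact contribute to component 1 only up to their last contact.

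### The structural MRI read for intercurrent stroke is limited to lesions under 10 days old, so no stated read captures older silent infarcts arising between scans

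*Protocol*

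**What the plan says.** Section 5d, part VI of the Protocol puts the aim and the rule in one sentence. The aim is that "Intercurrent stroke between scanning intervals will be diagnosed by 2 neurologists". The rule is that they do so "on inspection of FLAIR, T1 and T2 images for stroke < 10 days old". The next sentence adds that "DWI images will be inspected for recent stroke" and gives no age limit. The susceptibility-weighted sequence is acquired for microbleeds. Nothing elsewhere in the Protocol describes a read of infarcts 10 or more days old.

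Part VI then reduces the result to a yes/no variable that counts clinical and silent recurrences together. Section 5a (Timelines and feasibility) schedules the MRI: "At the 2 month, 4 month, and 1 year post-stroke time-points". Section 4c lists "Silent or recurrent brain infarction" among the secondary outcomes, and secondary hypotheses i and ii in section 4a use incident infarction at 4 months and 1 year. Section 8c, part ii models "silent/recurrent brain infarction (as defined in methods) as dependent variables", so the analysis rests on the definition in part VI.

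**The concern.** The purpose and the rule do not fit each other. A stroke that happened between two scans can be as old as the gap between them, roughly 61 days for the first interval and 244 for the second. An upper limit of 10 days on FLAIR, T1 and T2 excludes most of that range. DWI does not fill the gap, because its stated target is also recent stroke. The two reads overlap on fresh lesions and leave older ones to no one.

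Silent infarcts are what is at stake. A clinical recurrence can be learned of by other routes, but a silent one is known only from the scan. A reader who follows the text would record no event for a participant with an unmistakable new infarct several weeks old, and that entry would pass into the regression models of section 8c.

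**Working it through.** The Protocol states no detection figure, so there is nothing to reproduce. The check is how much of each scan interval the stated read covers.

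**Inputs**
- Scans at 2, 4 and 12 months (section 5a). With a month of 365.25/12 = 30.44 days, the intervals are 2 × 30.44 = 60.9 days and 8 × 30.44 = 243.5 days, together 304.4 days.
- Look-back on structural images: 10 days (section 5d, part VI).
- Look-back on DWI: not stated. Windows of 14, 21 and 30 days are tried as assumptions.
- New silent infarcts are assumed to arise at a constant rate.

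**Formula.** Share covered = look-back / interval. Pooled share = 2 × look-back / 304.4. For 10 days: 10/60.9 = 16.4%, 10/243.5 = 4.1%, 20/304.4 = 6.6%.

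| Look-back (days) | 2-4 months covered | 4-12 months covered | Pooled covered | Pooled missed |
|---|---|---|---|---|
| 10 (as written) | 16.4% | 4.1% | 6.6% | 93.4% |
| 14 (assumed) | 23.0% | 5.7% | 9.2% | 90.8% |
| 21 (assumed) | 34.5% | 8.6% | 13.8% | 86.2% |
| 30 (assumed) | 49.3% | 12.3% | 19.7% | 80.3% |

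If the structural read took in every lesion new since the previous scan, coverage would in principle be 100%.

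**Event counts (assumed risks, not in the Protocol).** If 10% of 120 participants had a new silent infarct over the 10 months, 12 events would become 12 × 0.066 = 0.8 with a 10-day window, or 12 × 0.197 = 2.4 with 30 days. At 20%, 24 events would become 1.6 or 4.7.

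**Visits are affected unequally.** Under a constant hazard the second interval carries four times the risk of the first (243.5/60.9 = 4). A fixed look-back would give the same expected number of silent events at both visits, so the repeated-measures model would see a flat pattern where the true one rises.

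**Bias or precision?** MRI reading is blinded (sections 5a and 5c), so a low detection rate should be the same in both arms.
- *As outcome.* Take assumed true risks of 10% and 5%. Multiplying each by 0.066 gives 0.66% and 0.33%. The risk ratio stays at 2.0, and the odds ratio moves only from (0.10/0.90)/(0.05/0.95) = 2.11 to 2.01. The risk difference shrinks from 5 to 0.33 percentage points.
- *As predictor.* With 10% true prevalence, missed cases are 10 × 0.934 = 9.34 per 100. The group recorded as free of infarction then holds 9.34/(90 + 9.34) = 9.4% misclassified, and a mean difference in brain volume would shrink by about 9%.

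The larger cost is therefore in events and precision.

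**The case against.** The strongest reply is that this is a slip of the sign. The sentence aims at stroke between scans, and DWI already handles fresh lesions. If the limit was meant to read more than 10 days, the two reads complement each other and nothing is lost. That is plausible and it stands, so the percentages above apply only if readers follow the text literally. It does not remove the point. Section 8c relies on the definition as printed, and nothing else in the Protocol corrects it. Nor can it be left to a statistical analysis plan as a detail not yet given, because the Protocol states a rule and that rule conflicts with its own aim.

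Three further replies also stand in part.
- DWI has no stated age limit, so a single figure of 93% is too firm. A range of 80-93% for look-backs of 10 to 30 days is fairer.
- The yes/no variable includes clinical recurrences, and section 7b records adverse events from consent to one year. A reader might infer that the whole outcome would be almost empty. The arithmetic covers silent events only, so the documents do not support that.
- A reader might infer that associations would be pulled materially toward the null. With blinded reading and few false positives, ratio measures barely move.

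It may also be said that two neurologists would compare each scan with the earlier one regardless. The Protocol does not say so. It gives an age limit instead.

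**Conclusion.** The point holds as an internal contradiction in section 5d, part VI that carries through to section 8c, part ii. Taken literally, the stated reads would miss about 93% of silent infarcts between scans with a 10-day look-back, and still about 80-91% if DWI reaches back 14 to 30 days. The loss in the 2-4 month interval alone is about 84% at 10 days. These figures assume a constant hazard and literal use of the age limit; if the sign is reversed, the loss is nil and only the text is wrong.

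The consequence is fewer silent events and less precision for a named secondary outcome. The documents do not support the stronger inference that the trial has deliberately chosen to ignore older infarcts, or that it certainly will. Brain volume as primary outcome, its ANCOVA and its sample size do not depend on this definition.

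**What to change.** In section 5d, part VI, remove or correct the 10-day limit and state the definition directly. For example: at the 4- and 12-month scans, an incident infarct is any lesion that the two blinded neurologists judge to be an infarct, as distinct from progression of white matter hyperintensity, and that is either new since the preceding study scan on FLAIR, T1 or T2 or present as a new lesion on DWI, whatever its age. Refer to this definition in section 8c, part ii.

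Two features matter. DWI should remain a detecting sequence, because a fresh lesion may be visible only there. White matter hyperintensity progression, which part VI measures separately, must be kept apart, because counting it as infarction would add false positives and these do bias a binary outcome. The 2-month scan has no preceding study scan and serves as the reference; that fits the hypotheses, which concern 4 months and 1 year.

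The cost is a wording amendment. The sequences, visits and two readers are already planned, and section 10d keeps the scans for 7 years, so any scan already read under the printed rule can be read again.
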